**Figure 2 Fig2:**
[figure not shown]
**The flowchart.**

### Data collection, quality, and monitoring

The personnel of the participating wards will not be involved in data collection. Instead, data collection will be performed by trained pharmacists and study assistants. Pharmacists will also perform telephone data collection at T2 and T3 and will not receive information about group affiliation of patients. To reduce selection bias, a standardized and scrupulously followed recruitment procedure will be employed, supervised by research assistants and monitored by the Clinical Trial Center North at the University Hospital Hamburg-Eppendorf (CTCN). Monitoring will be conducted according to the standard operation procedures of the Clinical Trial Center North and in compliance with the E6 ICH GCP guideline for good clinical practice. Clinical monitoring will also include review and resolution of missing or inconsistent results and source document checks (i.e., comparison of submitted study results to original reports) to assure the accuracy of the reported data.

### Statistical methods

The unit of inference will be the individual. Then, analyses will be carried out at cluster and at individual level. In a first simple approach, data in each cluster will be collapsed to construct a relevant summary measure (mean with standard deviation). This essentially removes the need to adjust for clustering effects. Of course, for variable-sized clusters, this analysis does neither take into account the intra-cluster correlation nor the cluster sizes and is less efficient than an individual-level analysis. But nevertheless, the relative simplicity of a cluster-level analysis still remains an advantage, albeit with some loss of efficiency and an inability to adjust for individual-level risk factors. In a second step, generalized estimating equations (GEE) models will be applied [60,61]. A generalized linear model takes into account within-group correlation and allows adjustment for the joint effects of cluster-level as well as individual-level factors without the requirement of parametric assumptions.

A model that takes into account the randomized clusters (wards) as random effect, with EQ-5D change or difference in prescribed long-term pharmaceutical agents between intervention and control at T3 as dependent and random group as independent variables, will be fitted to the data. In this model, baseline (T0) values of primary variables and a selection of further baseline characteristics of ward or patient will function as covariates. The intervention effects are quantified by the between-group differences of the corresponding estimates of changes from baseline from the fully adjusted model, which we assume to give the best account of the study results. In the statistical analyses, missing values will not be replaced. Methods for dealing with outliers will be defined in the statistical analysis plan (SAP) or in an addendum to the SAP. Secondary efficacy variables will be analyzed in an explorative way. Similarly, confidence intervals computed will be interpreted as interval estimates for presence or absence of effects in the study data. Intention-to-treat analyses will be performed.

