### Sample size

For the two independent primary outcomes of (1) health-related quality of life (EQ-5D) and (2) the difference in prescribed long-term pharmaceutical agents between intervention and control group at 12 months after discharge (T3), the following assumptions are made: for the single summary index of the five dimensions of the EQ-5D descriptive part (using reference value sets for Germany) for the changes from T0 to T3, a mean clinical relevant difference of 0.1 with standard deviation of 0.3 shall be demonstrated between intervention and control. For the difference in prescribed long-term pharmaceutical agents between both groups at 12 months after discharge (T3), a mean difference of 0.5 (number of agents) in reduction of agents with an expected standard deviation of about 1.5 has to be proven. If an EQ-5D difference of 0.1 with standard deviation of 0.3 (or a mean difference of 0.5 in reductions of agents with an expected threefold standard deviation) is to be demonstrated with a power of 80% at a significance level of 5% two-sided, a sample size of 143 per group will be required in a randomized trial. For the cluster randomized trial, this sample size has to be multiplied by a design factor of 5.4 [59] if an intra-class correlation coefficient (ICC) of 0.1 and a cluster size of 40 patients is assumed, resulting in a sample size of 1,545 evaluable patients in 38 clusters. Assuming a dropout rate of 5%, a total sample size of 1,626 patients in 42 wards has to be recruited initially. The number of patients per cluster was conservatively defined in order to cope with possible variations that could not be taken into account at the start of the trial. Therefore, sample size estimations will be verified by results of the baseline data analysis. If necessary, adjustments of sample size estimations will be realized. See Figure 2.

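### The flat rule against replacing missing values also covers baseline covariates, so the fully adjusted model would drop patients whose T3 result is known

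*Protocol article*

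**What the plan says.** All the elements stand in one section of the protocol article, Statistical methods.

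- **Outcome.** The ward random-effects model is fitted "with EQ-5D change or difference in prescribed long-term pharmaceutical agents between intervention and control at T3 as dependent". For EQ-5D this is explicitly a change score. For agents a change is implied, since the effects are read from "estimates of changes from baseline from the fully adjusted model, which we assume to give the best account of the study results" and the Sample size section speaks of reductions.
- **Covariates.** "baseline (T0) values of primary variables and a selection of further baseline characteristics of ward or patient will function as covariates".
- **Missing data.** "In the statistical analyses, missing values will not be replaced". No exception is made for baseline covariates. The sentence that follows defers methods for outliers to the SAP; missing values are not deferred.
- **Analysis principle.** "Intention-to-treat analyses will be performed".

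Table 1 lists EQ-5D at T0, T2 and T3, and the number of agents at all four time points.

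**The concern.** The point concerns patients whose T3 outcome is observed, not those lost to follow-up. A regression uses only rows in which every term has a value. If nothing may be filled, one gap at T0 removes the patient from the model that the authors regard as their best account of the results. The plural in the covariate sentence may mean that both T0 values enter both models. In that case a missing T0 EQ-5D would also remove the patient from the agents analysis.

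Three things are at stake. Observed outcomes would be discarded without need, against the intention-to-treat aim. The analysed set would depend on which covariates are selected. Those dropped may differ from those kept.

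**Working it through.** **1. The plan's own figures.** The Sample size section assumes "a mean clinical relevant difference of 0.1 with standard deviation of 0.3 shall be demonstrated between intervention and control" for EQ-5D and "a mean difference of 0.5 (number of agents) in reduction of agents with an expected standard deviation of about 1.5" for agents. Both give a standardised difference of 1/3.

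- Normal approximation: n = 2 × (1.960 + 0.842)² × 3² = 141.3, so 142 per group.
- With the t distribution, 142 gives 79.9% power and 143 gives 80.2%. This agrees with "with a power of 80% at a significance level of 5% two-sided, a sample size of 143 per group will be required".
- 2 × 143 × 5.4 = 1,544.4, so 1,545 evaluable, as stated.
- 1,545 / 0.95 = 1,626.3, against 1,626 stated. The dropout allowance is 1,626 − 1,545 = 81 patients.

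The factor 5.4 is taken as stated. (The usual formula with ICC 0.1 and 40 per cluster gives 1 + 39 × 0.1 = 4.9; that is a separate matter.)

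**2. Patients lost through baseline gaps.** The article gives neither the number of covariates k nor their missing rate p, so both are assumptions. With independent gaps the share retained is (1 − p)^k.

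| k | p | Retained | N of 1,545 | Lost |
|---|---|---|---|---|
| 1 | 1% | 0.990 | 1,530 | 15 |
| 3 | 2% | 0.941 | 1,454 | 91 |
| 5 | 2% | 0.904 | 1,397 | 148 |
| 10 | 2% | 0.817 | 1,262 | 283 |

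If the gaps fall in the same patients, the loss is smaller. With five items at 2% and complete overlap it is 0.02 × 1,545 = 31 instead of 148.

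**3. Effect on power, five items at 2%, EQ-5D.**

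- 38 clusters that simply become smaller, ICC 0.1. Before: 1,545/38 = 40.7 per cluster, design effect 1 + 39.7 × 0.1 = 4.97, power 83.6%. After: 1,397/38 = 36.8 per cluster, design effect 4.58, effective size 1,397/4.58/2 ≈ 152.6 per arm, power 82.9%.
- Design factor held at 5.4: power falls from 80.5% to 76.4%. This overstates the loss, because the design effect shrinks with the clusters.

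**4. Change score or T3 value.** The linear model (Y3 − Y0) = a + b·arm + c·Y0 is the same as Y3 = a + b·arm + (c + 1)·Y0, so b is unchanged. Moving to T3 therefore costs nothing. Alone it also rescues nobody, because a patient without Y0 still lacks a covariate. It helps only together with filling, since the dependent variable is then always an observed value.

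**The case against.** The best defence is that the loss may be very small.

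- Five or more long-term drugs is an entry criterion, so the T0 agent count will rarely be unknown.
- Ward characteristics are hardly ever missing.
- Trained pharmacists and study assistants collect the data, and monitoring includes resolving missing results.
- Patients must be able to consent and to take their own medication, which screens out many who could not answer a questionnaire.
- The SAP, which is not shown, could choose only complete covariates.

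All of this stands as to size. It does not remove the rule, which is fixed in the article without exception, and T0 EQ-5D is a covariate whatever else is selected.

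A reader might infer more than the documents support:

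- **That the result will be biased.** If missingness depends on the modelled covariates and not on the outcome given them, a correctly specified complete-case regression remains consistent. Being too ill at T0 could be largely such a mechanism.
- **That the change score is the cause.** Step 4 of the working shows that it is not.
- **That adjusted and unadjusted results cannot be compared.** The article defines no unadjusted individual-level model. An unadjusted analysis of EQ-5D change would need T0 as well.
- **That the 5% allowance is meant to cover baseline gaps.** It is labelled dropout and nothing more.

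**Conclusion.** The point holds in a limited form. Deletion is not stated in words, but it follows from a rule without exceptions applied to a model that needs T0 values and further baseline characteristics. It sits badly with the intention-to-treat aim.

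Its size cannot be determined from the article. Under the assumed rates it runs from about 15 patients (one item at 1%) to about 148 (five items at 2%, independent gaps). The low end is plausible, given the safeguards. Power is not the issue: about 0.7 percentage points in the five-item case. Selection is a possibility, not a finding. This is an inexpensive improvement to the plan, not a threat to the trial's conclusions.

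**What to change.** In the Statistical methods section or the SAP:

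1. Limit the no-replacement rule to outcome values.
2. Model the T3 value with T0 as covariate; the arm coefficient is the same as in the change model.
3. Fill missing baseline covariates by a prespecified method blind to arm and outcome: the overall mean plus a missing indicator for continuous items, or a separate category for missing in categorical ones.
4. Keep every patient with a T3 value in the primary set.
5. Report T0 missingness by arm, and give the complete-case result as a sensitivity analysis.

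The cost is a few sentences and little programming. There is also a statistical cost. Adjustment is weaker for patients with filled values, which matters most for T0 EQ-5D. Moreover, wards are randomised before patients of the intervention period are recruited, and T0 is collected unblinded. If T0 values or their missingness differ by arm, filling can introduce some bias of its own. That is why item 5 belongs to the change.

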**Primary outcomes**					
Health-related quality of life	EQ-5D	X		X	X
Difference in the number of prescribed long-term pharmaceutical agents	Number of prescribed long-term pharmaceutical agents	X	X	X	X

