#### Points of measurement

Prior to the intervention, baseline data will be collected. During the following intervention period, for each patient of the intervention and control group, primary outcomes will be measured at four points in time: at admission to (T0) and discharge from hospital (T1) as well as 6 and 12 months after discharge from the hospital (T2 and T3).

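### Both primary outcomes are modelled at T3 only with nothing replaced, so patients without a T3 value drop out even when T2 was measured, and deaths have no stated handling

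*Protocol article*

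**What the plan says.** All references are to the protocol article.

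- **Model.** Statistical methods plans a mixed model in which the ward is the random effect. Its outcome and group variable are set out thus: "with EQ-5D change or difference in prescribed long-term pharmaceutical agents between intervention and control at T3 as dependent and random group as independent variables". Each patient contributes one outcome value, at T3.
- **Covariates.** In that model, "baseline (T0) values of primary variables and a selection of further baseline characteristics of ward or patient will function as covariates". No T1 or T2 value enters.
- **Missing data.** "In the statistical analyses, missing values will not be replaced". The section leaves the handling of outliers to the SAP, but not this rule.
- **Analysis set.** "Intention-to-treat analyses will be performed", with no definition of the set.
- **Other steps.** The ward-mean analysis uses whatever values are observed. The GEE step is described for correlation within groups, not for repeated visits by one patient.
- **Data available.** Table 1 schedules EQ-5D at T0, T2 and T3, and the "number of prescribed long-term pharmaceutical agents" at T0, T1, T2 and T3. Deaths are recorded at T1, T2 and T3 (Table 1; Stopping rules). Statistical methods gives neither T2 nor death a role in the primary analysis.
- **Expected loss.** Sample size counts evaluable patients and then inflates: "Assuming a dropout rate of 5" per cent.

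**The concern.** The patients are at least 65, multimorbid, on five or more long-term drugs, and followed for 12 months after a hospital stay. Some will die or be lost between T2 and T3, and those who deteriorate after discharge are plausibly over-represented among them. A model of T3 alone ignores the T2 value that would show this deterioration.

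Death raises a second problem. The Background cites evidence that reducing drugs can lower mortality, death is a secondary outcome, and a difference in deaths can go to the safety board. The plan thus allows for an effect on who is alive at T3. If there is one, the survivors in the two arms are not like for like, and the plan does not say that its T3 contrast is a contrast among survivors.

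What is at stake is the meaning and possible bias of both primary estimates, rather than their precision.

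**Working it through.** **1. The plan's own figure.** A difference of 0.1 with SD 0.3 (or 0.5 with SD 1.5) at 80% power and 5% two-sided needs 143 per group by the t-test. Then 2 × 143 × 5.4 = 1,544.4, rounded up to 1,545 evaluable, and 1,545 / 0.95 = 1,626.3, against the stated 1,626. The figure reproduces with the printed factor of 5.4. (The stated ICC and ward size give 1 + 39 × 0.1 = 4.9; that is a separate matter and does not affect this point.)

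**2. Who is analysed.** One T3 outcome per patient, baseline covariates only and no replacement mean that a patient without T3 contributes nothing to the treatment contrast. The article does not say this in words; it follows from the three statements together.

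**3. When that is harmless.** If T3 missingness depends only on arm and the covariates in the model, a correctly specified T3 model is unbiased. If it depends on T2 status given those covariates, it can be biased.

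**4. Shift from unequal loss.** Suppose lost patients are worse by the same amount D in both arms. Then

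shift = (difference in loss rates) × D.

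The documents give neither input, so both are assumed:

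| Difference in loss | D = 0.1 | D = 0.6 |
|---|---|---|
| 2 points (e.g. 6% v 4%, mean 5%) | 0.002 | 0.012 |
| 5 points (e.g. 15% v 10%) | 0.005 | 0.030 |

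That is 2% to 30% of the 0.1 target. The sign depends on which arm loses more: a completers' difference of 0.10 becomes 0.07 for all patients if the intervention arm loses 5 points more and D = 0.6, and 0.13 in the reverse case. A 5-point gap fits a mean loss of 5% only as 7.5% v 2.5%. D = 0.6 is roughly what results from valuing death at 0 against an assumed mean index near 0.6.

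**5. Loss that depends on T2.** Simulation with a true EQ-5D difference of 0.10, SD 0.3, T2–T3 correlation 0.5 to 0.7, and 15% to 21% missing at T3 (all assumed except 0.10 and 0.3):

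| Loss depends on T2 in | T3-only difference | Using T2 as well |
|---|---|---|
| both arms equally | 0.094–0.097 | 0.100–0.101 |
| control only | 0.057–0.070 | 0.100–0.101 |
| intervention only | 0.125–0.133 | 0.100–0.101 |

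The last column is the T3 contrast corrected through the regression of T3 on T2, which is what a likelihood-based model of both visits does. The agent outcome has the same ratio of difference to SD (0.5/1.5 = 0.1/0.3). With the same correlation and the same dependence per SD, the T3-only results scale by 5: 0.47–0.485, 0.285–0.35 and 0.625–0.665 against a true 0.5.

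**6. Power.** With 1,626 patients in 42 equal wards and ICC 0.1, 5% loss leaves 1,626 × 0.95 / 42 = 36.8 per ward and a design effect of 1 + 35.8 × 0.1 = 4.58. Power (t with 40 df) is 0.848. At 20% loss it is 0.835 and at 40% it is 0.808. Because the wards stay in the trial, losing patients within them costs little.

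**The case against.** **The no-replacement rule is not itself the error.** This stands. A mixed model of T2 and T3 replaces nothing and complies with it. The weakness is the combination of that rule with a model of T3 alone.

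**Intention-to-treat may still be correct.** A reader might infer that the label is false. The documents do not support that: the term is undefined there, and it can mean analysing patients according to how their ward was randomised. Nor would the mixed model include everyone, since a patient with neither T2 nor T3 adds nothing to it. What can be said is that not all included patients are analysed.

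**Baseline adjustment covers much of the mechanism.** This also stands. Loss related to health or drug burden at admission is largely handled by the T0 covariates. Only dependence on what happens after baseline remains.

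**The figures are assumed.** True. The only documented loss is 5%; the simulated 15% to 21% is well above it. When the dependence on T2 is equal in both arms the distortion is small, and the large values need a dependence in one arm only, for which the documents give no evidence.

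**A mixed model does not solve deaths.** Correct. EQ-5D and agent count are undefined after death, and a missing-at-random model implicitly projects values for patients who have died. Deaths need their own statement.

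**This could be left to the SAP.** Sensitivity analyses could be. The primary model and the missing-value rule could not be treated as open, because the article states both.

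**Conclusion.** The point holds in a limited form. As written, both primary analyses use only patients with a T3 value and ignore T2 data that will be in hand. The estimate is unbiased if T3 missingness depends only on arm and baseline covariates. It can be biased if missingness depends on post-baseline status, and it is a comparison among survivors that is not declared as such.

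It would be tempting to conclude that the primary results will be materially biased. The documents do not show that. Under loss differences of 2 to 5 points and lost patients 0.1 to 0.6 worse, the EQ-5D shift is 0.002 to 0.03 in either direction. The upper end comes close to valuing death at 0, and there the gap is between two estimands and not simply a bias in one. Power is hardly affected. The case for change is that the better analysis uses data already planned and costs little.

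**What to change.** 1. Make the primary analysis of each outcome a linear mixed model of T2 and T3 together, with the T0 value as covariate, arm × time, a random effect for the randomised unit (which may be several wards, as those sharing a senior physician are randomised together), and correlation between visits within patient. The T3 contrast is the primary estimate. No values are replaced, every patient with T2 or T3 is included, and the result is valid under missing at random.
2. State how deaths are handled for each outcome. For EQ-5D, for example, add a sensitivity analysis that sets the index to 0 from death, labelled as a different estimand. For agent count, declare a while-alive or survivor estimand.
3. Define the intention-to-treat set, and report deaths and loss by arm beside the primary result.

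The cost is revised wording and slightly more modelling and programming. No further data are needed.

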### Stopping rules

Data on death (T1, T2, T3) and hospital re-admissions (T2, T3) of the included patients will be collected. If significant differences in the re-admission rate or number of deaths will be discovered, the safety board will be informed to decide whether to stop or continue the trial.

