### Recruitment

Each week, up to 30 eligible patients will be recruited per hospital consecutively at admission. Pharmacists will inform about the study and will seek written informed consent. Recruitment will be stopped as soon as the necessary number of patients per week is reached.

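### The safety board is to be informed once a difference in deaths or re-admissions is significant, an undefined and insensitive gate for safety review

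*Protocol article*

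**What the plan says.** The protocol article's Stopping rules section consists of two sentences. The first fixes the data: "Data on death (T1, T2, T3) and hospital re-admissions (T2, T3) of the included patients will be collected". The second fixes the trigger: "If significant differences in the re-admission rate or number of deaths will be discovered, the safety board will be informed to decide" whether the trial stops or continues. The article describes no other flow of data to the board.

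Other sections bear on this rule:

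- **Blinding:** statisticians, study assistants, physicians and patients are not blinded. Pharmacists are blinded only for data collection at T2 and T3.
- **Points of measurement:** T1 is discharge. T2 and T3 are 6 and 12 months after discharge.
- **Sample size:** the only significance level in the article, "with a power of 80% at a significance level of 5% two-sided", is set for the two primary outcomes. The ICC assumption, "an intra-class correlation coefficient (ICC) of 0.1 and a cluster size of 40 patients is assumed", belongs to them as well.
- **Statistical methods:** cluster summaries, GEE and a ward random effect are planned for the main analysis. Secondary efficacy variables are to be analysed exploratively. Neither statement is linked to the safety comparison.
- **Recruitment:** "Each week, up to 30 eligible patients will be recruited per hospital consecutively at admission".

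**The concern.** A safety board exists to judge evidence that is still uncertain. Here the stated condition for informing it is that the evidence has already passed a significance test, and the people who apply that test belong to an unblinded trial team. An excess of deaths that is worrying but not yet significant would not trigger notification under the rule as written. Naming a test and a level in another document would not cure this, because the gate itself would remain.

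Two things add to the problem. First, the word significant has no defined operating characteristics here: no test, level, schedule of looks or treatment of wards is given for this comparison. Second, re-admissions are not collected before T2. The intervention is delivered during the hospital stay, so a re-admission signal protects new patients only if recruitment is still running when it appears. This is the only safety rule the article states, in a trial of patients aged 65 and over on five or more long-term drugs in which drugs are proposed for stopping.

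**Working it through.** **The plan's own figures.** The stopping rule contains no number to reproduce. The sample size that sets the scale of the safety comparison can be checked:

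- From "a mean clinical relevant difference of 0.1 with standard deviation of 0.3", the normal approximation gives 142 per group and the t-based value is 142.2, in line with "a sample size of 143 per group will be required in a randomized trial".
- 2 × 143 × 5.4 = 1,544.4 (stated 1,545).
- 1,545 / 0.95 = 1,626.3 (stated 1,626).

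The factor 5.4 does not follow from the stated cluster size and ICC, since 1 + 39 × 0.1 = 4.9. That is a separate matter and is not used below.

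**1. Chance that a real excess of deaths is flagged.** Event rates and ICC for deaths are not in the article, so the following are assumptions: 8% against 12% deaths, ICC 0.01, a ward-adjusted two-sided 5% test. Size: 1,626 / 42 = 38.7, taken as 39 patients per ward and 21 wards per arm, so 819 per arm at full information.

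DE = 1 + (m − 1) × 0.01; n_eff = n / DE; SE = √[(0.08 × 0.92 + 0.12 × 0.88) / n_eff] = √(0.1792 / n_eff); power = Φ(0.04 / SE − 1.96).

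| Information | n per arm | m | DE | n_eff | 0.04 / SE | Power |
|---|---|---|---|---|---|---|
| One quarter | 204.75 | 9.75 | 1.0875 | 188.3 | 1.30 | 25% |
| One half | 409.5 | 19.5 | 1.185 | 345.6 | 1.76 | 42% |
| Full | 819 | 39 | 1.38 | 593.5 | 2.30 | 63% |

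Each row is a single look. In a simulation of the same scenario with four ward-adjusted looks at an unadjusted level, 70% of trials were flagged at some look.

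**Range.** With 772 evaluable patients per arm, DE = 1 + 39 × ICC, ICC from 0 to 0.1 and assumed control death rates of 5% to 10%, full-data power is:

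- relative risk 1.25: 7% to 34%
- relative risk 1.5: 15% to 84%
- relative risk 2.0: 39% to nearly 100%

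With half the patients observed to T2, and half the 12-month risk accrued by then, power is 8% to 30% for relative risk 1.5 and 19% to 75% for relative risk 2.0. For re-admissions at assumed control rates of 30% to 50%, relative risk 1.25 has 29% to nearly 100% power at full data.

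**2. False-alarm rate.** If a nominal 5% test ignored wards, the rate at one look would be 2 × [1 − Φ(1.96 / √DE)], with m = 40:

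- ICC 0.01 (assumed): DE = 1.39, rate 9.6%
- ICC 0.05 (assumed): DE = 2.95, rate 25.4%

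Simulation with 20 wards of 40 patients per arm gave 9.9% and 25.1%. A cluster-level t-test in the same simulation gave 4.5% to 6% at one look for one outcome. With five looks at both outcomes and no adjustment of the level, it gave 17% to 26%. The rate therefore depends on choices that the article does not state.

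**3. Timing.** At the weekly cap, four hospitals recruit 120 patients a week: 1,626 / 120 = 13.6 weeks. If only two sites recruited (an assumption), 1,626 / 60 = 27.1 weeks. The first T2 data come about 26 weeks after the first discharge. At the cap, recruitment could thus end before, or at about the same time as, the first re-admission data.

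**The case against.** **The test is not described, so it cannot be called wrong.** This stands. A reader might infer that the trigger is an unadjusted 5% test applied repeatedly, with an inflated error rate. The article states neither an unadjusted test nor a number of looks, and its main analysis takes account of wards. Test, level and schedule are commonly left to an SAP or board charter, so their absence alone is no finding. The supported statement is that the error rate is undefined in this document.

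**Most real harm would not be missed.** This stands too. A reader might infer that from the interim figures, but the 8% v 12% example gives 63% at full information at a single look, and a doubling of deaths would usually be found at full data with a small ICC. All these figures rest on rates outside the article.

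**Too many alarms and too few cannot both hold.** They cannot hold for one test. They describe two readings of an undefined rule: ignoring wards gives extra alarms, while a ward-adjusted test is often silent at interim. They should not be added together.

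**A false alarm costs little.** Largely correct: the trigger leads to board review, not to an automatic stop. The weight of the point therefore lies on missed and late signals.

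**The board may see data in other ways.** Possible. The rule does not say that this is the only occasion, and the article mentions external monitoring under GCP. But that monitoring concerns recruitment procedure and data accuracy, and no reporting by arm to the board is described.

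**Recruitment will not run at the cap.** Fair. A reader might infer that re-admission signals will come after recruitment has ended; the text supports only that they could. Slower recruitment weakens the point, deaths at T1 are an earlier signal, and it is unclear whether patients from the six-month baseline period count towards the 1,626.

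**Conclusion.** The point holds in limited form. As written, notification of the board depends on a significant difference, and the article describes no other reporting to the board. That is a rule fixed badly rather than a detail left out, because defining the test elsewhere would leave the gate in place.

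Its size depends on assumptions. At 8% against 12% deaths and ICC 0.01, a look at one quarter or half of the information would more often than not leave the board uninformed. For smaller excesses (relative risk 1.25 at control rates of 5% to 10%), even the full data would usually do so. Large excesses with little clustering would usually be flagged by the end. The false-alarm rate cannot be determined from the article. The ICC of 0.1 is stated for the primary outcomes and should not be carried over to deaths or re-admissions as fact. A late re-admission signal is a possibility at the recruitment cap, not a prediction.

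The rule should be changed: it is the only safety rule stated, and the change is cheap.

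**What to change.** Remove significance as the precondition for informing the board. State instead that the existing board receives deaths and re-admissions by arm, with ward-adjusted confidence intervals, at pre-set dates during recruitment and follow-up, whatever the result.

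If a formal flag is kept, make it an additional alert. Compute it with a ward-aware method and state its level and the planned looks, including how the two outcomes share that level. The decision to stop or continue stays with the board.

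The cost is a revised paragraph and a short recurring table. No further patients are needed.
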